### **7.1. TMS INTERVENTION**

All patients included in the study will receive TMS and speech therapy.

- TMS: TMS is a technique for electrical stimulation of brain tissue through the generation of a magnetic field, modulating neuronal activity at the

stimulation site and interconnected neural networks. The study will use transcranial magnetic stimulation (TMS) delivered with a figure-of-eight coil guided by neuronavigation. An intermittent theta-burst stimulation (iTBS) protocol will be applied, following current clinical practice guidelines and recommendations for TMS (Lefaucheur et al., 2020). The theta-burst protocol allows for shorter stimulation times (<10 minutes per session) with effects comparable to traditional repetitive stimulation protocols. Neuronavigation, based on the patient's own MRI, ensures accurate targeting of the stimulation area, reducing inter- and intra-individual variability. Treatment will be applied to the left dorsolateral prefrontal cortex. Each patient will receive 10 consecutive sessions during the first 2 weeks, followed by 1 weekly session until completing 6 months of treatment.

- Sham TMS: For the sham TMS group, a sham coil indistinguishable from the therapeutic coil will be used. Sessions will occur at the same frequency as the active TMS group, ensuring that patients remain unaware of whether they are receiving sham or standard TMS. Only the staff responsible for administering the TMS will know the treatment assignment.
- Blinding: The evaluator conducting follow-up assessments will be blinded to the treatment allocation (active or sham TMS). Only the technician applying the TMS will know whether the treatment is active or sham.
- If a patient misses a scheduled TMS or speech therapy session, it will be rescheduled, preferably within the same week. If the treatment cannot be performed that week, the missed sessions will be scheduled for the following weeks (with one additional session per week). The maximum period without treatment sessions will be 4 weeks. If this period is exceeded, the patient will be withdrawn from the study.

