#### 251   **5.4. WITHDRAWAL CRITERIA**

252   All randomized patients will be included in the intention-to-treat analysis. The

253   sponsor and/or investigator may withdraw any participant from the clinical trial if

254   they meet any of the following withdrawal criteria:

- 255       1. Any condition that disrupts the study procedures.
- 256       2. Onset of severe depression.

3. The patient's own decision to withdraw.
4. Serious adverse events related to the treatment and study therapies.
5. Any cause resulting in the interruption of treatment for more than 4 weeks.
6. Patients undergoing chemotherapy.
7. Pregnancy.
8. Meeting any of the following exclusion criteria during the study:
  - a. Presence of contraindications related to the treatments being used.
  - b. Major psychiatric disorders (e.g., schizophrenia, schizoaffective disorders, bipolar disorder, or obsessive-compulsive disorders).
9. At the investigator's discretion and with confirmation from the sponsor.

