## **5.6. MANAGEMENT OF WITHDRAWALS/DISCONTINUATIONS**

After withdrawal from the study, patients will continue receiving standard clinical care for PPA. Withdrawn patients will not be replaced.

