## **16. STATISTICAL ANALYSIS**

### **16.1. DESCRIPTION OF THE STATISTICAL ANALYSIS**

All statistical analysis will be performed by intention-to-treat. The safety analysis will include all patients who have received at least one dose of treatment or one cycle of TMS.

For the analysis of normality and equality of variances of continuous variables, the Shapiro-Wilk test and Levene's test will be used, respectively. Quantitative variables will be presented as mean and standard deviation and will be compared using the Student's t-test or non-parametric test where appropriate. Qualitative variables will be expressed as frequency and percentage and compared using the  $\chi^2$  test and Fisher's exact test when at least 25% of the cells in the contingency table show an absolute frequency of less than 5.

The primary analysis will be the difference in brain metabolism in the region of interest involved in the disease between the two treatment arms at 6 months. A statistical analysis will be used with a p-value <0.05 (two-tailed). The same analysis will be used to evaluate the change in the secondary outcomes of the study.

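### Stopping treatment is treated as leaving the study, so no 6-month PET is planned for withdrawn patients although all randomised patients are promised an intention-to-treat analysis

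*Protocol*

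**What the plan says.** **Withdrawal.** Section 7.1 allows at most 4 weeks without sessions and continues: "If this period is exceeded, the patient will be withdrawn from the study". Section 5.4 says the sponsor or investigator *may* withdraw a participant from the trial if "they meet any of the following withdrawal criteria". Its list includes "Any cause resulting in the interruption of treatment for more than 4 weeks", "Onset of severe depression" and "Serious adverse events related to the treatment and study therapies".

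**After withdrawal.** Section 5.6 says "After withdrawal from the study, patients will continue receiving standard clinical care for PPA". It names no further study visit or scan and rules out replacement. No section distinguishes a patient who stops treatment from one who stops follow-up.

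**Endpoint timing.** Section 14 defines the primary variable as the change in regional cerebral metabolism from baseline to the final visit. Sections 12 and 13.3 schedule FDG-PET at those two points only. Section 12 (Final Visit) also requires the final assessments within 15 days of the last treatment session.

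**Analysis.** Section 5.4 opens with "All randomized patients will be included in the intention-to-treat analysis", and section 16.1 says "All statistical analysis will be performed by intention-to-treat".

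**The concern.** An intention-to-treat comparison needs outcome data on the patients who were randomised, including those who stopped treatment. Here the event that ends treatment also ends planned data collection, and the primary endpoint has no intermediate measurement to fall back on. The promise in sections 5.4 and 16.1 therefore cannot be met with observed primary data for anyone who is withdrawn.

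The reasons for leaving may be related to treatment or outcome. Related serious adverse events could differ between active and sham stimulation. Section 2 says that the feasibility of long-term treatment is unknown given frequent behavioural symptoms, especially in the semantic variant. If those who leave differ in prognosis and leave at different rates in the two arms, the comparison of scanned patients no longer has the protection of randomisation.

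This is a matter of what the protocol arranges to collect. A statistical analysis plan can specify how missing scans are handled, but it cannot recover scans that were never taken.

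**Working it through.** **1. The rules side by side**

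- On the 4-week interruption, section 5.4 makes withdrawal optional (*may*) and section 7.1 makes it mandatory (*will*). The two must be reconciled.
- Severe depression and related serious adverse events appear only in section 5.4, under *may*.
- A patient removed under section 7.1 is more than 28 days past the last session, so the 15-day window for final assessments has already closed, by at least 28 − 15 = 13 days.
- With PET only at baseline and the final visit, such a patient has one scan and no change score.

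**2. The plan's own sample-size figure**

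The sample size calculation (numbered 15.2, within section 16) needs 54 participants and allows 10% dropout: 54 / 0.90 = 60, which reproduces. The primary comparison is thus sized on 54 patients with outcome data out of 60 randomised.

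**3. Target effect and an implied SD**

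- Target: 20% of the stated 6-month decline, 0.20 × 167.78 = 33.56 units. (The printed regression gives 74.82 + 15.16 × 6 = 165.78 and a target of 33.16; the difference is immaterial here.)
- The protocol states neither SD nor power. Assuming 80% power, two-sided 0.05 and 2:1 allocation (36 and 18 patients), the SD that yields 54 is 33.56 / [(1.960 + 0.842) × √(1/36 + 1/18)] = 41.5. At an assumed 90% power it is 35.9.

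**4. Bias from comparing only scanned patients (illustrative assumptions)**

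Let w be the withdrawal rate in an arm and g the extra decline of withdrawn patients over those who stay, the same in both arms. The mean decline of all patients in an arm is the stayers' mean plus w × g. The comparison of stayers is therefore off by (w_active − w_sham) × g.

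| Withdrawal, active / sham | g = 0.5 SD (20.7) | g = 1 SD (41.5) |
|---|---|---|
| 10% / 10% | 0 | 0 |
| 15% / 5% | 2.1 (6%) | 4.1 (12%) |
| 20% / 10% | 2.1 (6%) | 4.1 (12%) |
| 20% / 5% | 3.1 (9%) | 6.2 (19%) |

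Percentages are of the 33.56-unit target. Reversing the arms reverses the sign. With 40 active and 20 sham patients, the unequal rows mean 7, 10 and 9 withdrawals in total, above the planned 6. A 15-point difference is also possible with exactly 6, in either direction: 6 of 40 against 0 of 20 (15% against 0%), or 2 of 40 against 4 of 20 (5% against 20%).

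**5. A change in the effect being estimated**

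If withdrawn active patients lost all benefit (an extreme assumption), the effect in all randomised patients would be 33.56 × (1 − w): 30.2 units at 10% withdrawal and 26.8 at 20%. An analysis of scanned patients would still aim at 33.6.

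**6. Precision**

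With SD 41.5 and a true difference of 33.56, power is about 84% with 60 analysed, 80% with 54 and 75% with 48. With all 60 scanned but the effect diluted to 30.2, the standardised difference is 30.2 / [41.5 × √(1/40 + 1/20)] = 2.66, and power is about 76%. Full follow-up therefore need not raise power; its purpose is validity.

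**The case against.** Several stronger readings are tempting, and the documents do not support them.

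- **A reader might infer that every patient with severe depression or a related serious event leaves.** Section 5.4 makes this discretionary, and section 5.3 allows SSRIs to be added during the study. Only the 4-week rule in section 7.1 is mandatory, and it applies after missed sessions have been rescheduled where possible.
- **A reader might infer that the 6-month NPI loses the patients who worsened most.** Depression is one of 12 NPI domains, withdrawal for it is optional, and worsening in the other domains is not in itself a listed ground.
- **A reader might conclude that the analysis must be one of completers.** Section 5.6 is silent on later assessments and does not forbid them, and handling of missing data can be left to an analysis plan that is not at hand. The supportable statement is that no later scan is planned.
- **A reader might assume a much larger bias.** Taking half the projected decline as the gap (167.78 / 2 = 84 units) with a 10-point difference in withdrawal gives 0.10 × 84 = 8.4 units, 25% of target. But 84 / 41.5 is about 2 SD, and nothing in the documents supports a gap that wide.

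It is also fair to say that the sample size already allows for 10% loss, that some of those patients will withdraw consent whatever the wording, and that nothing in the documents shows that withdrawal will differ between arms. All of this limits the size of the problem. It does not remove the conflict between mandatory removal from the study and an analysis of all randomised patients.

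**Conclusion.** The concern holds in a limited form. The protocol treats stopping treatment as leaving the study, plans no primary outcome for withdrawn patients, and still promises an intention-to-treat analysis of all randomised patients. Removal is certain only under the 4-week rule in section 7.1, which itself conflicts with section 5.4; for severe depression and related serious events it is possible. Unless missing scans are imputed, the primary comparison is restricted to patients who stay in.

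The likely size is modest: zero with equal withdrawal rates and prognosis, and about 2 to 6 units (6–19% of the 33.6-unit target) under the unequal scenarios above, direction unknown. This rests on assumed withdrawal rates, an assumed prognosis gap and an SD of about 41.5 back-solved at an assumed 80% power. The scans cannot be obtained afterwards and the remedy is mostly wording, so this is a cheap improvement to make before patients are lost.

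**What to change.** - In sections 5.4, 5.6 and 7.1, separate discontinuing study treatment from withdrawing from the study. Leave the treatment-stopping triggers unchanged.
- Reconcile *may* in section 5.4 with *will* in section 7.1 for the 4-week interruption.
- State that every randomised patient who still consents to follow-up, and for whom the procedures remain appropriate, has the remaining assessments and the 6-month PET on the originally scheduled date and is analysed as randomised. The proviso on procedures is needed because, for example, pregnancy is one of the listed withdrawal grounds.
- Amend the 15-day window in section 12 (Final Visit) to match, so that the final assessments of a patient who has stopped treatment follow the original schedule rather than the last session.

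**Cost.** Protocol wording, plus a few final visits and scans within the planned 60 patients (about 6 at most if losses run at the planned 10%). The downside is that off-treatment data may dilute the on-treatment effect. That is inherent in the intention-to-treat comparison the protocol already promises.

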## 7.2 SPEECH THERAPY INTERVENTION

We will use a treatment previously shown to be effective in PPA, which incorporates a modified hierarchy of steps from the Arizona Naming Cascade (Grasso et al., under review; Henry et al., 2013; 2019; Kim, 2017).

The treatment focuses on naming through guided retrieval of residual semantic, phonological, and orthographic information, with the aim of retraining specific vocabulary and teaching strategies to facilitate broader word retrieval. These strategies include semantic circumlocution and using knowledge of word form for self-cuing.

|                                              |
|----------------------------------------------|
| Table 3. Summary of Naming Hierarchy for PPA |
|----------------------------------------------|

|                                  |                                                                                                                                     |
|----------------------------------|-------------------------------------------------------------------------------------------------------------------------------------|
| Semantic Feature Analysis        | 
Prompt semantic description with “Tell me about it.”
 
Summary of the description
 
Recall the picture
             |
| Orthographic /Phonemic Self-Cue  | 
Written production of the target word, “Can you write the word?”
 
“Can you say the first sound?”
                       |
| Written                          | Request repeated copy of written word (x3)                                                                                          |
| Semantic plausibility judgments  | Ask yes/no questions regarding semantic features of target (x5)                                                                     |
| Recall                           | 
Ask for recall of two semantic features plus spoken/written name
 
Ask for name and write the picture
                   |
| Description of a complex picture | 
Provide a complex image with the target included in the scene
 
“Describe the picture using the word we are practicing”
 |

328

329 During the first 2 weeks, the patient will receive 4 speech therapy sessions.  
330 Subsequently, each patient will receive 1 session per week. The speech therapy  
331 sessions will take place immediately after the TMS session.

## 332 **8. CONCOMITANT MEDICATION**

333 There is no medication incompatible with this clinical trial.

## 334 **9. TREATMENT ALLOCATION**

335 Patient inclusion in the study will be consecutive. A prospective record will be  
336 maintained for all subjects who are not included in the study, specifying the  
337 reason for exclusion. All patients aged 18 or older diagnosed with PPA according to  
338 the 2011 consensus criteria by Gorno-Tempini et al., who meet the inclusion  
339 criteria, do not meet any exclusion criteria, and have signed the informed consent  
340 form, will be invited to participate.

341 Once patients are included in the study, they will be randomized to one of the  
342 treatment arms using computerized randomization. Each patient will be assigned  
343 a unique numeric code for identification. Randomization will be stratified by the  
344 clinical subtype of PPA (non-fluent, semantic, and logopenic).

If a patient meets the study's eligibility criteria, the investigator will provide detailed information about the study, addressing all questions and concerns. The patient will then be given the informed consent form to review at their convenience and discuss with family or friends if necessary. If the patient agrees to participate, both the patient and the informing investigator will sign two copies of the consent form. One copy will be given to the patient, and the other will be filed in the investigator's study archive.

Once the patient is enrolled in the study, the investigator will log into the study's electronic CRF using their personal credentials to complete the inclusion process and perform the randomization. At this stage, the patient will be assigned a unique code for the study and allocated to one of the treatment arms.

## **10. BLINDING**

The study is designed as a double-blind clinical trial, the patient will remain unaware of the neuromodulation treatment being received at any time (active TMS or sham TMS).

## **11. UNBLINDING AND EMERGENCY PROCEDURES**

Unblinding will only occur if the patient experiences an emergency where knowledge of the study treatment received is necessary to guide medical decisions.

If a patient meets the criteria for unblinding, the PI may access the treatment allocation by completing the "Unblinding" form in the electronic case report form (eCRF).

## **12. DATA COLLECTION AND MONITORING**

### **I. Baseline Visit**

At the Cognitive Neurology Clinic of Hospital Clínico San Carlos, patients who meet the eligibility criteria will receive both verbal and written information about the study. They will have the opportunity to ask any questions, as well as consult with their family and/or friends regarding their decision to participate.

If the patient decides to participate, two copies of the informed consent form will be signed—one will be given to the patient, and the other will be filed in the investigator's study archive. Participation in the study will also be documented in the patient's medical record, including the date of inclusion, the version of the signed consent form, and confirmation that a copy was provided to the patient.

The patient will be assigned a unique study code and randomized via the eCRF system.

380 During the Baseline Visit, the following activities will be performed:

- 381 ✓ Evaluation of inclusion and exclusion criteria.
- 382 ✓ Delivery of the patient information sheet and informed consent form.
- 383 ✓ Randomization.
- 384 ✓ Clinical Information: Date of birth, sex, years of formal education, year of
- 385 PPA diagnosis, and relevant medical history.
- 386 ✓ Concomitant Medication: Details of current medications.

387 The patient will be provided with a patient diary to record adverse events, visits to  
388 other specialists, and/or any required healthcare services. This diary is intended to  
389 assist the patient in adhering to treatment routines and facilitate study  
390 participation. The information recorded in the diary will be verified by a member of  
391 the research team and documented in the patient's medical records and eCRF  
392 during study visits.

393 After this visit, treatment appointments will be scheduled to ensure compliance  
394 with the established timeframes. The treatment initiation (corresponding to the  
395 relevant phase) must occur within 30 days following Visit 1 (Baseline Visit).

## 396 **II. Visit 1 (Baseline Visit, Before Initiating the Intervention)**

397

- 398 ✓ During the baseline visit, the patient will undergo evaluations according to
- 399 the following activities:
- 400 ✓ Demographic Data
- 401 ✓ Language and General Cognitive Evaluation
- 402 ✓ MLSE (Mini Linguistic State Examination)
- 403 ✓ Trained word naming
- 404 ✓ Spontaneous speech (words per minute)
- 405 ✓ IDDD (Interview for deterioration in Daily living Activities in Dementia)
- 406 ✓ NPI (Neuropsychiatric Inventory)
- 407 ✓ Patient Diary Review
- 408 ✓ Concomitant Medication Review
- 409 ✓ PET-FDG (Positron Emission Tomography with Fluorodeoxyglucose)

410 The visit may be conducted over a maximum of three days to prevent patient  
411 fatigue.

412 Language and general cognitive assessments may also be conducted within the  
413 three months preceding the start of treatment.

## 414 **III. Intermediate Visit (+3 months after the start of the intervention)**

415 During this visit, the patient will be evaluated following this schedule of activities:

- 416 ✓ MLSE
- 417 ✓ Trained Word Naming
- 418 ✓ Spontaneous Speech (Words per Minute)
- 419 ✓ IDDD
- 420 ✓ NPI
- 421 ✓ Patient Diary Review
- 422 ✓ Concomitant Medication Review

423

#### 424 **IV. Final Visit (+6 months after the start of the intervention)**

425 During the final visit, the patient will be evaluated following this schedule of  
426 activities:

- 427 ✓ MLSE
- 428 ✓ Trained Word Naming
- 429 ✓ Spontaneous Speech (Words per Minute)
- 430 ✓ IDDD
- 431 ✓ NPI
- 432 ✓ Patient Diary Review
- 433 ✓ Concomitant Medication Review
- 434 ✓ PET-FDG

435 The visit may be conducted over a maximum of three days to prevent patient  
436 fatigue.

437 The assessments will be completed within the following 15 days after the last  
438 treatment session.

### 439 **13. ASSESSMENTS**

#### 440 **13.1. Baseline Visit**

- 441 - Age
- 442 - Sex
- 443 - Years of formal education
- 444 - Languages spoken and age of acquisition
- 445 - Mother tongue
- 446 - Laterality
- 447 - Family history of neurodegenerative diseases

448 - Duration of symptom

449 - Language assessment: Different tasks that assess language domains: Cookie  
450 Theft picture; Paradis narrative sequence picture; reading narrative text, words,  
451 capitalized words, foreign words, and non-words; omission of initial phoneme;  
452 spelling words; repetition of words, non-words, syllables and sentences; semantic  
453 association; naming pictures and actions; word-picture matching; synonyms;  
454 picture-action matching; orophonatory praxis; verb tense agreement; sentence  
455 comprehension.

456 - Cognitive assessment: Test included in NEURONORMA protocol (Peña-  
457 Casanova et al., 2009): memory span (forward and backward digit spans), the  
458 Corsi block-tapping test, Trail Making Test (TMT), Symbol Digit Modalities Test  
459 (SDMT), Visual Object and Space Perception Battery (VOSP; subtests for object  
460 decision, progressive silhouettes, position discrimination, and number location),  
461 Judgement of Line Orientation (JLO), Tower of London-Drexel University, Rey-  
462 Osterrieth Complex Figure Test (copy and memory), and Stroop Color-Word  
463 Interference Test.

464 - Addenbrooke's cognitive examination III (ACE-III): ACE-III is a general cognitive  
465 screening tool that assesses attention (temporal spatial orientation, 3-item  
466 registration, serial subtractions) memory (recall of 3 items, anterograde memory  
467 of a name and address, retrograde memory, and recall and recognition of a name  
468 and address) verbal fluency (words beginning with "p" and animals), language  
469 (comprehension of a complex command, sentence writing, single word repetition,  
470 proverb repetition, a 10-item confrontation naming task, a semantic task, and  
471 reading) and visuospatial skills (copy of intersecting infinity loops, copy of a cube,  
472 drawing of a clock, counting dots, and identifying incomplete letters).

473 **13.2. Visit 1, 2 and 3 (week 0, week 12 and week 24)**

474 - Mini-Linguistic state examination (MLSE)

475 The MLSE is a brief screening tool designed to assess language impairments in  
476 various neurodegenerative disorders, particularly in PPA. It includes a series of  
477 tasks that evaluate different language processes: naming, syllable repetition,  
478 repeat and point, non-word repetition, semantic association, sentence  
479 comprehension, reading, sentence repetition, writing, and picture description.  
480 These tasks are grouped in five language domains: motor, phonology, semantics,  
481 syntax, and working memory, and scoring is done by classifying the errors made by  
482 the subject. The time of administration is approximately 20 min.

483 - Naming of trained words

484 A list of 261 words from 8 different semantic categories: animals, food, objects,  
485 places, furniture, clothing, transportation, and body parts. Two consecutive  
486 sessions of oral naming of the list were conducted.

487 - Words per minute in spontaneous speech

488 The patient was shown a wordless book (Frog stories) and was asked to describe  
489 the story in detail for 3 minutes. The number of words per minute was calculated.

490 - Interview for Deterioration in Daily Life in Dementia (IDDD)

491 IDDD is a scale designed to assess functional decline in daily and instrumental  
492 activities. It is a caregiver-administered tool.

493 - Neuropsychiatric Inventory (NPI)

494 It is a caregiver-administered tool designed to assess neuropsychiatric symptoms.  
495 The NPI assesses 12 different symptom domains, which include: delusions,  
496 hallucinations, agitation/aggression, dysphoria/depression, anxiety,  
497 euphoria/elation, apathy/indifference, disinhibition, irritability/lability, aberrant  
498 motor behaviors, night-time behavioral disturbances and appetite/eating  
499 disturbances.

